## Abstract

**Introduction:**

Diagnosing asthma requires confirmation by bronchodilator reversibility (BDR) with or without bronchial provocation testing (BPT). Despite being needed in 80% of suspected cases following BDR, BPT access remains limited in Canada. Type-2 (T2) inflammatory biomarkers (fractional exhaled nitric oxide (FeNO) and blood eosinophil count (BEC)) may be underutilised for BPT prioritisation and are insufficiently studied to support asthma diagnosis in real-world primary care, especially in children. We aimed to explore whether T2 biomarker-based prioritisation of BPT reduces diagnostic delays, and improves triage efficiency and guidance based on exacerbation risk.

**Methods and analysis:**

Three academic centres in Québec will measure inflammatory biomarkers alongside BDR and/or BPT interpretation for patients with suspected asthma referred by primary care providers (PROPULSION SANTÉ, NCT06981169). Consenting patients aged ≥6 years will undergo FeNO, BEC and BDR testing. If BDR is non-diagnostic, subsequent BPT will be prioritised for patients with ≥1 elevated biomarker (BEC ≥300 /µL, (FeNO ≥25 ppb if ≥12 years or FeNO ≥20 ppb if <12 years)); others will follow usual timelines. Reports to the referring healthcare providers will include standard interpretation of BDR/BPT and biomarker results to state exacerbation risk and suggested corticosteroid dosage. Asthma control and quality of life will be assessed at baseline and remotely at 4, 8 and 12 months. The primary outcome will be the delay from the reception of test request for the diagnosis of asthma patients with versus without elevated biomarker(s). Secondary outcomes include biomarkers’ diagnostic performance, asthma control, quality of life, health benefits, cost-effectiveness, environmental impact and patient satisfaction. We aim to recruit 1500 patients to PROPULSION SANTÉ, with optional biobanking for translational sub-studies for 123 adults (DIVE, NCT05992519) and 123 children (DIVE2, NCT07011394).

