European guidelines recently incorporated FeNO as an effective alternative and cost-effective diagnostic tool for asthma and to optimise access to specialised testing : a FeNO level ≥40 ppb is 90% specific for asthma diagnosis in adults.^29 30^ The United Kingdom’s National Institute for Health and Care Excellence (NICE) guidelines recommend using FeNO and BEC early in the diagnostic algorithm as a first-line diagnostic tool before spirometry or peak flow monitoring.^29 30^ In children ≥5 years, only FeNO (≥35 ppb) has been validated as a first-line diagnostic test, while BEC had been used after BDR and PEF, along with skin prick tests or specific IgE measurement.^29 31^ The introduction of FeNO testing as a first-line diagnostic tool is estimated to enable approximately 29 000 additional asthma diagnoses annually, leading to earlier treatment initiation, improved disease control, reduced absenteeism and potential cost savings of £100–204 million per year.^32^

In Quebec, over 3000 diagnostic tests are still pending across Centre Hospitalier Universitaire de Sherbrooke (CHUS), CHU Sainte-Justine (CHUSJ) and the Montreal Children’s Hospital (MHC), including 1300 tests for children, with wait times exceeding 1 year. BPTs are scheduled chronologically, with priority only for internal referrals, that is, for specialists of the institution. The lack of robust prospective data on FeNO and eosinophils (and limited FeNO access) has restricted their integration into diagnostic algorithms.

Our overarching aim is to address an evidence gap by evaluating the integration of inflammatory biomarkers into referral for the asthma diagnosis specifically from primary or community care under real-world conditions. Specifically, we aim to assess whether FeNO and BEC can improve the prioritisation of patients for bronchial provocation testing (BPT), thereby streamlining referrals and supporting more timely and cost-effective asthma diagnosis. Propulsion Santé also includes two translational sub-studies: DIVE (in adults) and DIVE-2 (in children) involving additional sampling (serum and nasal epithelial lining fluid (NELF)) to link inflammatory mediators (alarmins, interleukins and eicosanoids), diagnosis and T2 biomarkers to gain mechanistic insight at the point of diagnosis in primary care.

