### Intervention

The interpretation of respiratory function tests and biomarkers will be performed by the principal investigator pulmonologist at each centre or by trained designated collaborating pulmonologists by following these models:

High-risk inflammatory asthma is defined by FeNO ≥25 ppb or BEC ≥300 cells/µL in participants ≥12 years (≥20 ppb or ≥300 cells/µL in children aged 6 to <12 years)^15 50^ : one or more elevated biomarkers will be interpreted as a high risk of asthma exacerbation. If spirometry is non-diagnostic, BPT will be prioritised (<2–4 weeks).Low risk inflammatory asthma is defined by FeNO <25 ppb and BEC <300 cells/µL (<20 ppb or <300 cells/µL in children aged 6–<12 years)^15 50^: this will be interpreted as a low risk of asthma exacerbation. If spirometry is non-diagnostic, BPT will be scheduled according to the standard waiting list.

Results of biomarkers will be integrated on the medical report indicating the probability (high/low) of asthma exacerbation and suggested management with either ICS taken as-needed (T2-low) or regularly (T2-High) ICS if clinically appropriate, which will be forwarded to the referring physician.

The patient test pathway based on their respiratory test and the results of the inflammometry assessment is summarised in figure 2.

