### Discussion

This study addresses a critical gap in the literature by prospectively evaluating the implementation of inflammatory biomarkers in a real-world primary care referral pathway across both adult and paediatric populations. Beyond its scientific contribution, our protocol will optimise clinical resources by reducing the backlog of approximately 3000 respiratory function tests, currently awaiting completion across the three participating centres, through the engagement of study-dedicated respiratory therapists.

We anticipate that this study will demonstrate the utility of inflammatory biomarkers as effective triage and prioritise instruments for BPT. Given the high rate of false positives in respiratory testing as well as the substantial rate of clinical misclassification in Canada (between 33% and 45% in adults and children),^20 22^ our study will calculate optimal biomarker thresholds to achieve 90% specificity, positive predictive value (PPV) exceeding 80% and LR+ greater than 10—parameters essential for reliable diagnostic confirmation.^57^ In effect, this strategy sacrifices sensitivity in favour of specificity, leading to high PPV and LR+.

Existing literature supports the relevance of our approach. Li *et al* conducted a large retrospective cohort study involving 7463 adult patients with suspected asthma in secondary care. Among the 2349 patients with complete biomarker data, concurrent elevation of FeNO (> 40 ppb) and BEC (>0.3×10ˆ9 cells/L) was associated with a diagnostic specificity greater than 95%.^58^ Similarly, Nekoee *et al* demonstrated that combining biomarkers with spirometry improved diagnostic accuracy (AUC 0.82, 95% CI 0.78 to 0.86),^59^ reinforcing the relevance of inflammometry in routine assessment. Additionally, the predictive value of both BEC and FeNO has been demonstrated in adults,^812 15 16 19 60^,^70^ and to a lesser extent in the paediatric^50^ populations, with significant clinical implications for early intervention and treatment adjustment. Furthermore, these biomarkers are valuable tools for therapeutic decision-making, as elevated values are associated with a better response to anti-inflammatory therapies.^71^,^75^ As modifiable indicators, the inflammatory signals provided by BEC and FeNO highlight the importance of early measurement to better prioritise patients requiring timely inflammation control.^15 61 62 64^

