We acknowledge potential methodological limitations. The multicentre design necessitates rigorous harmonisation of practices across sites. The risk of missing data—especially in paediatric patients due to refusal of blood sampling or difficulty in FeNO measurement among children aged 6–8 years—is a concern; this will be minimised by offering a relatively painless capillary blood sampling (which has shown a failure rate below 5%)^76^ or by applying topical analgesia for venipuncture. For FeNO, success rates increase from approximately 40% at age 5 to nearly 100% by age 10.^42 77^ Additionally, the use of 6-s FeNO measurements is expected to further improve feasibility in children aged 6–8 years. Sensitivity analyses using FeNO or blood eosinophils alone will reflect what can be achieved in real-world conditions if one of the biomarkers is not available. Additional limitations include the intrinsic variability of biomarkers related to recent infections or medication use, management of comorbidities that may influence biomarkers and the complexity of economic evaluation across different centres. Nonetheless, this diversity enhances the generalisability of findings across Quebec and potentially other Canadian provinces. Our findings must be contextualised within the evolving landscape of precision medicine in respiratory care. Pavord *et al* have emphasised the clinical and economic benefits of biomarker-guided treatment algorithms in severe asthma, demonstrating reduced exacerbations and improved quality of life through targeted biological therapies.^61^ Similarly, the CAPTAIN study highlighted how biomarker stratification can predict treatment response, potentially transforming clinical decision-making from earlier disease stages.^71^ In this way, our approach brings the principles of precision medicine into the diagnostic process by focusing on identifiable and modifiable traits in an understudied population, that is, individuals with predominantly non-severe asthma issued from the primary/community care. It helps reduce uncertainty in asthma diagnosis by moving from a standard approach to a more personalised assessment using early measurable biological markers.^78^

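### The primary high-versus-low delay contrast is largely set by the booking rule itself, and no comparison with the planned pre-project baseline is defined

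*Protocol article*

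**What the plan says.** The aim (Abstract, Introduction) is to "explore whether T2 biomarker-based prioritisation of BPT reduces diagnostic delays". The primary outcome (Abstract, Methods and analysis) is the "delay from the reception of test request for the diagnosis of asthma patients with versus without elevated biomarker(s".

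The Intervention section fixes the waits. For patients with one or more raised biomarkers: "If spirometry is non-diagnostic, BPT will be prioritised (<2–4 weeks". For the others: "If spirometry is non-diagnostic, BPT will be scheduled according to the standard waiting list". The Introduction describes the existing lists as chronological, "with wait times exceeding 1 year".

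Statistical methods specifies a mixed model whose group term is high-risk versus low-risk, with study period and number of tests waiting as fixed effects. The same paragraph says that a pre-project baseline delay will be established and that delays will be monitored overall and by inflammatory status.

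The Discussion expects the backlog to fall "through the engagement of study-dedicated respiratory therapists". It also says of the single-marker analyses: "Sensitivity analyses using FeNO or blood eosinophils alone will reflect what can be achieved in real-world conditions". That sentence is conditional on one of the two markers being unavailable.

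**The concern.** The aim asks what prioritisation does to delay. The primary contrast compares two groups inside the prioritised pathway, and the protocol assigns their waits by the same variable that defines the groups. No concurrent T2-high group goes without prioritisation, so the contrast does not isolate the gain even for T2-high patients. If provocation-test slots are limited, part of the contrast may be time added to T2-low waits, and that part has the same sign as a benefit.

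At stake is what the main result can support. The key-message box and the Conclusion look to shorter delays and a change of diagnostic pathway. A large high-versus-low difference would be compatible with an overall gain, no overall change, or a loss for T2-low patients.

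**Working it through.** **1. The plan's own figure.** Sample size gives f = 0.07 for N = 1500, alpha 5%, power 80% and correlation 0.5. For a between-groups factor with k groups and m measurements, λ = f²·N·m / [1 + (m − 1)ρ], with df (k − 1, N − k). The article gives neither k nor m. Solving for f at 80% power gives 0.0695 for k = 3, m = 2; 0.0697 for k = 4, m = 3; and 0.0627 for k = 2, m = 2. So 0.07 is attainable but not uniquely reproducible. It is used below only for scale.

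**2. Contrast produced by the rule.** Inputs: usual wait 52 weeks (a lower bound, from the Introduction, taken here as the BPT wait); T2-high wait 2–4 weeks (Intervention); non-diagnostic spirometry 80%, or 60% as in children (Introduction), assumed equal in both groups. Time before the biomarker visit is taken as common to both groups.

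- 80%: 0.8 × (52 − 4) = 38.4 to 0.8 × (52 − 2) = 40 weeks
- 60%: 0.6 × (52 − 4) = 28.8 to 0.6 × (52 − 2) = 30 weeks

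For scale, f = 0.07 with two equal groups is d = 2 × 0.07 = 0.14. For an assumed SD of 13 to 52 weeks that is 1.8 to 7.3 weeks.

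**3. What the contrast contains.** Let both groups wait W under chronological booking, and H and L under the rule. Then L − H = (W − H) + (L − W): T2-high gain plus T2-low loss. With H pinned at 2–4 weeks, each extra week of T2-low BPT waiting adds 0.6–0.8 week to the contrast.

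Illustration with assumed values: W = 12 months, H = 0.7 month, half of patients T2-high.

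| Assumption | T2-low wait (months) | Contrast (months) |
|---|---|---|
| T2-low unaffected | 12 | 11.3 |
| Fixed capacity, half the queue enrolled: 0.25 × 0.7 + 0.75x = 12 | 15.8 | 15.1 |
| Fixed capacity, whole queue enrolled: 0.5 × 0.7 + 0.5x = 12 | 23.3 | 22.6 |

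In the two fixed-capacity rows the overall mean stays at 12 months.

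**4. A closed queue without pinned waits.** Assume 1000 waiting and 20 slots a week, so 50 weeks to clear and a chronological mean of 25. With T2-high first and T2-high share p, H = 25p and L = 50p + 25(1 − p), so L − H = 25 for any p. At p = 0.3, 0.5 and 0.7 the T2-high gain is 17.5, 12.5 and 7.5 weeks and the T2-low loss 7.5, 12.5 and 17.5. The contrast is 1.4 to 3.3 times the T2-high gain, and the overall mean stays at 25.

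**5. Added capacity.** A simulated open queue assumed a backlog of 1000, 20 arrivals a week, half T2-high, everyone under the rule. Mean waits of first-year arrivals:

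- 20 slots a week, chronological: 50.1 weeks in both groups
- 30 slots, chronological: about 24.8 weeks overall
- 30 slots, T2-high first: 4.1 (T2-high) and 37.2 (T2-low) weeks

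Against the 20-slot baseline, T2-low patients look 50.1 − 37.2 = 12.9 weeks better off. Against the same capacity in chronological order they lose 37.2 − 24.8 = 12.4 weeks. A baseline comparison that ignores throughput can hide displacement.

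**6. Baseline and outcome side by side.** The baseline (Statistical methods) runs to performance of the requested test. The outcome (Primary Outcome) runs to the last confirmatory test. For a patient who needs reversibility testing and then BPT, these can be different dates. Biomarkers are measured at study visits (Study design), so no T2 split of the baseline is described.

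**7. Single-marker analyses.** Booking uses the either-marker rule. Where both markers were measured, the share of the FeNO-low group prioritised on eosinophils is [P(BEC+) − P(both)] / [1 − P(FeNO+)]. The article gives no prevalences. Assuming FeNO raised in 35–45%, eosinophils in 35–40% and both in 15–25%, the share runs from (0.35 − 0.25)/0.65 = 15% to (0.40 − 0.15)/0.55 = 45%.

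**The case against.** The rule acts only after non-diagnostic reversibility testing. Patients diagnosed by spirometry, or sent straight to provocation testing (Figure 2 legend), are outside it, and the clock starts at the request, before biomarkers are known. Whether centres with year-long lists can deliver the early slot is a real feasibility question. This stands. A reader might infer that significance is guaranteed and that the result says nothing about the aim, but the documents support only that significance is near certain if the rule is followed and that the contrast is partial evidence.

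The plan collects a baseline, monitors delay overall and by status, and adjusts for queue length. This also stands. A reader might infer that harm to T2-low patients will inevitably pass as benefit, but that monitoring could reveal it. What the plan does not state is a contrast against the baseline. The detail might sit in a fuller document, but the article does fix the primary contrast as high versus low, and its two end-point definitions differ.

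The 22.6-month contrast needs fixed capacity and a fully enrolled queue. The Discussion expects the backlog to fall, and Sample size sets 1500 participants against about 3000 pending tests. It is an upper illustration only.

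On single markers, a reader might infer that the Discussion sentence is simply wrong. Its condition covers patients lacking one marker, in whom only the available marker can trigger priority. The objection applies only where both were measured.

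Finally, replacing the primary contrast outright is debatable, since calendar time and added staff confound a before-and-during comparison.

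**Conclusion.** The point holds in limited form. The primary contrast is largely the booking rule and cannot by itself show that prioritisation shortens diagnostic delay. On the Introduction's figures the rule-made part is about 29–40 weeks, with 52 weeks as the usual BPT wait and equal non-diagnostic shares in the two groups.

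With T2-high waits held at 2–4 weeks, lengthened T2-low waits widen the contrast. If T2-high waits are not held, the closed queue shows the contrast can stay constant while its make-up shifts from gain to displacement. The size of any displacement cannot be derived from the article: capacity, enrolled share and T2-high share among suspected cases are not given. The 15–45% mixing in the single-marker analyses rests on assumed prevalences.

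**What to change.** - Interpret high versus low as a process (adherence) measure.
- Pre-specify two comparisons with the same start and end points in both periods: (a) delay in all patients needing provocation testing, study period versus pre-implementation; (b) T2-low delay versus the pooled pre-implementation delay, as a displacement estimate.
- Account for test throughput where counts are available. State that calendar time and the added therapists limit causal attribution to the biomarkers.
- In the single-marker analyses, where both markers were measured, exclude patients prioritised on the other marker or use both-low as comparator. Limit the Discussion statement to patients in whom only one marker was available.

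The cost is mainly wording and two defined contrasts on a baseline already planned, plus test counts, which the article does not say are held. The price in inference is calendar-time confounding and a more modest claim.

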**Ethics and dissemination:**

Study protocols were ethically approved CIUSSS de l'Estrie–CHUS #MP-31-2025-5593/MP-31-2024-5346; 2023–4791). Results will be communicated and submitted to peer-reviewed journals.

**Trial registration number:**

ClinicalTrials.gov (NCT06981169; NCT05992519; NCT07011394).

WHAT IS ALREADY KNOWN ON THIS TOPICAsthma diagnosis faces critical access barriers despite its high prevalence. Type-2 inflammatory biomarkers effectively predict disease risk and treatment response in asthma, but are not specific for asthma: they remain underutilised in primary care and in diagnostic settings.WHAT THIS STUDY ADDSThis study evaluates whether biomarker-based patient prioritisation can overcome diagnostic constraints by streamlining the testing pathway to earlier asthma diagnosis and enhancing interpretation reports with individualised risk estimates, potentially supporting the early identification of patients with high-risk asthma.HOW THIS STUDY MIGHT AFFECT RESEARCH, PRACTICE OR POLICYFindings could transform the asthma diagnostic pathway and management strategies by establishing a more efficient and personalised approach that prioritises limited diagnostic resources toward high-risk patients. This may reduce delays, enhance the appropriateness of testing and support more sustainable care by limiting unnecessary procedures.

## Introduction

Asthma is among the most prevalent chronic diseases worldwide and the most common in children.^1^ In Quebec, around 10% of the population—approximately 900 000 individuals, including 300 000 children—are affected.^2 3^ Asthma is a major cause of absenteeism, healthcare expenditures and morbidity, placing a significant burden on both the healthcare system and society; yet it remains disproportionately under-researched.^4 5^

Characterised by airway inflammation and bronchial hyper-responsiveness, asthma causes nonspecific and variable symptoms, complicating diagnosis.^6^ The disease is heterogeneous, comprising several phenotypes and endotypes.^7^ In the era of precision medicine, identifying type 2 (T2) inflammation – present in half of asthmatics – is particularly important.^8 9^

T2 inflammation is mediated by T-helper type 2 (Th2) lymphocytes and group 2 innate lymphoid cells (ILC2), which secrete interleukin (IL)−4, IL-5 and IL-13, promoting eosinophil recruitment, mucus hypersecretion and is associated with epithelial damage. Non-invasive biomarkers, such as fractional exhaled nitric oxide (FeNO) and blood eosinophil count (BEC), reflect IL-4/IL-13 and IL-5 activity, respectively.^9^,^14^ Both are linked to poor prognosis and may be used to predict asthma exacerbations and accelerated lung function decline.^15 16^ In adults, the ORACLE-2 meta-analysis showed that FeNO >25 parts per billion (ppb) and BEC >300/μL are linked to increased risk of exacerbations.^15^ In children over 6 years, post-hoc analysis from the VOYAGE study found that FeNO >20 ppb and BEC >300/μL predicted higher rates of severe exacerbations.^17^,^19^

Objective testing is essential for accurate asthma diagnosis, especially given high rates of overdiagnosis estimated at 33% in adults and 44% in children in Canada.^20^ Relying on subjective clinical criteria for asthma diagnosis has led to disease overestimation, impacting treatment decisions and healthcare resources.^21^ Spirometry is recommended to demonstrate post-bronchodilator reversibility (BDR), an increase in forced expiratory volume in 1 s (FEV1) ≥200 mL and ≥12% in adults and ≥12% in children and adolescents).^6^ However, spirometry is inconclusive in up to 80% of cases (and over 60% in children), necessitating a methacholine bronchial provocation test (BPT).^22 23^ Furthermore, identifying post-bronchodilator reversibility is of doubtful clinical consequence, as associated with other diseases (eg, chronic obstructive pulmonary disease) and unrelated to the risk of asthma attacks.^24 25^

Methacholine BPT is a relatively cumbersome procedure, requiring monitoring by specialised hospital units and significant testing time, which limits accessibility. These constraints contribute to both over-diagnosis and under-diagnosis, with significant individual, societal, environmental and economic consequences.^1421 26^,^28^

Inadequate access to objective tools in primary care delays or impairs treatment, worsening asthma control, quality of life and healthcare costs.^6 21^ Zafari *et al* estimated that improved diagnostic algorithms reducing sub-optimal asthma control by 10% could save $50.5 billion over 20 years in Canada.^4^

European guidelines recently incorporated FeNO as an effective alternative and cost-effective diagnostic tool for asthma and to optimise access to specialised testing : a FeNO level ≥40 ppb is 90% specific for asthma diagnosis in adults.^29 30^ The United Kingdom’s National Institute for Health and Care Excellence (NICE) guidelines recommend using FeNO and BEC early in the diagnostic algorithm as a first-line diagnostic tool before spirometry or peak flow monitoring.^29 30^ In children ≥5 years, only FeNO (≥35 ppb) has been validated as a first-line diagnostic test, while BEC had been used after BDR and PEF, along with skin prick tests or specific IgE measurement.^29 31^ The introduction of FeNO testing as a first-line diagnostic tool is estimated to enable approximately 29 000 additional asthma diagnoses annually, leading to earlier treatment initiation, improved disease control, reduced absenteeism and potential cost savings of £100–204 million per year.^32^

In Quebec, over 3000 diagnostic tests are still pending across Centre Hospitalier Universitaire de Sherbrooke (CHUS), CHU Sainte-Justine (CHUSJ) and the Montreal Children’s Hospital (MHC), including 1300 tests for children, with wait times exceeding 1 year. BPTs are scheduled chronologically, with priority only for internal referrals, that is, for specialists of the institution. The lack of robust prospective data on FeNO and eosinophils (and limited FeNO access) has restricted their integration into diagnostic algorithms.

Our overarching aim is to address an evidence gap by evaluating the integration of inflammatory biomarkers into referral for the asthma diagnosis specifically from primary or community care under real-world conditions. Specifically, we aim to assess whether FeNO and BEC can improve the prioritisation of patients for bronchial provocation testing (BPT), thereby streamlining referrals and supporting more timely and cost-effective asthma diagnosis. Propulsion Santé also includes two translational sub-studies: DIVE (in adults) and DIVE-2 (in children) involving additional sampling (serum and nasal epithelial lining fluid (NELF)) to link inflammatory mediators (alarmins, interleukins and eicosanoids), diagnosis and T2 biomarkers to gain mechanistic insight at the point of diagnosis in primary care.

